### 4.2. Outcomes of Research and Next Steps

If the Flourishing Child Intervention is assessed as acceptable and feasible by parents, it will provide accessible means for parents to gauge their child’s mental and physical health and engage targeted support when needed. The next phase of this project will test the effectiveness of the intervention in improving parent outcomes and early childhood flourishing. Insights gained through the feasibility trial will inform amendments to recruitment strategies, methods for maximising adherence and completion rates, data screening processes, and delivery of the intervention. Results from focus groups, questionnaires, and website metrics will inform refinements of the intervention itself to maximise utility and reduce participant burden.

Subsequent research will focus on implementing the intervention at scale in different geographical settings and with different population groups, initially in Western Australia. This will involve co-design with local consumers and contextual and cultural adaptation, ensuring acceptability and feasibility among different populations, including Culturally and Linguistically Diverse (CALD) families, Aboriginal and Torres Strait Islanders, families with neurodiverse children, and other groups [13]. In scaling up this digital intervention, the research team will contextualise the geographical region and local population, including digital access, literacy, and connectivity.

Future research will include a cost-effectiveness analysis comparing those who utilise the Pathway Tool and those who do not, as well as health service utilisation and associated costs. Project impacts will incorporate key recommendations to be articulated in a policy briefing paper. Findings will be disseminated widely through publications and stakeholder presentations.

Early childhood parenting interventions have tended to focus on reducing child problem behaviours [16,19,24]. The Flourishing Intervention is unique in its focus on enhancing the positive aspects of a child’s life. The Flourishing Intervention has the potential to increase parents’ awareness of their children’s strengths and support needs, and confidence in supporting them to flourish. According to the Logic Model provided in Figure 1, we anticipate the potential for long-term positive impacts as a result of parents engaging with the Flourishing Intervention (such as reduced incidence of mental health issues in children).

## Figures and Tables

**Figure 1 children-13-00581-f001:**
[figure not shown]
Logic model for the flourishing child.

**Figure 2 children-13-00581-f002:**
[figure not shown]
Screenshot of the Pathway Tool homepage.

**Figure 3 children-13-00581-f003:**
[figure not shown]
Visual summary of data triangulation.

**Table 1 children-13-00581-t001:** Schedule of enrolment, interventions, and assessments.

	STUDY PERIOD							
	Enrolment	Allocation	Post-Allocation					Close-Out
TIMEPOINT	−*t* _1_	0	*t* _1_	*t* _2_	*t* _3_	*t* _4_	*t* _5_	*t_x_*
**ENROLMENT**:								
Eligibility screen	X							
Informed consent	X							
Allocation		X						
**INTERVENTIONS**:								
Intervention Group								
Flourishing Check			X		X ^†^			
Pathway Tool								
Waitlist Control Group								
Flourishing Check			X		X ^†^			
Pathway Tool			X **—————————————→** X					X
**ASSESSMENTS**:								
Demographics			X					
Flourishing Check Acceptability and Feasibility Questionnaire ^†^			X					
Pathway Tool Acceptability and Feasibility Questionnaire ^×^*				X				
Focus groups *						X		
Perceived self-efficacy in recognising and supporting flourishing in early childhood ^×^			X				X	
Perceived knowledge of how and when to seek support ^×^			X				X	
Engagement with and participation in supports relevant to flourishing in the early years ^×^			X				X	
Mental Health Continuum–Short Form (MHC-SF)			X				X	
Paediatric Quality of Life (PedsQL)			X				X	

* Only the intervention group will complete these assessments. ^×^ Can be found in Section S3 and S4 of the Supplementary Materials. ^†^ Can be found in Section S5 of the Supplementary Materials. The analysis plan and results pertaining to these measures (i.e., test–retest reliability measured at T3 and Flourishing Check Acceptability and Feasibility Questionnaire measured at T1) will be detailed in a separate paper explaining the development of the Flourishing Check.

**Table 2 children-13-00581-t002:** Description of Pathway tool engagement metrics.

Engagement Type	Engagement Category	Metric	Description
Passive Information Access	Exploratory Engagement	Level 1–A resource clicked within the Pathway Tool Level 2–Participant follows link to external resource	An indicator over two levels that the participant finds the resource engaging and relevant
Active Information Access	Recurring Engagement	Total number of resources saved	An indicator that participant is interested in engaging with the resource more than once
Community Participation	Collaborative Engagement	A resource link copied to share	An indicator that the participant wants others in the community to engage with the resource

**Table 3 children-13-00581-t003:** Data triangulation process and criteria used to assess feasibility and acceptability.

	Red (Do Not Proceed to Full-Scale RCT)	Amber (Consider Proceeding to Full-Scale Trial Only After Intervention and Protocols Have Been Refined)	Green (Proceed to Full-Scale RCT Without Refinement)
Flourishing Check	<40% of participants rated all key acceptability items as ≥4 AND Focus groups revealed repeated themes of low to moderate acceptability	40–60% of participants rated all key acceptability items as ≥4 AND Focus groups revealed repeated themes of moderate to high acceptability	>60% of participants rated all key acceptability items as ≥4 AND Focus groups revealed repeated themes of high acceptability
Pathway Tool	<40% of participants rated all key acceptability items as ≥4 AND Focus groups revealed repeated themes of low to moderate acceptability	40–60% of participants rated all key acceptability items as ≥4 AND Focus groups revealed repeated themes of moderate to high acceptability	>60% of participants rated all key acceptability items as ≥4 AND Focus groups revealed repeated themes of high acceptability
Flourishing Check	<40% of participants rated all key feasibility items as ≥4 AND Focus groups revealed repeated themes of low to moderate feasibility	40–60% of participants rated all key feasibility items as ≥4 AND Focus groups revealed repeated themes of moderate to high feasibility	>60% of participants rated all key feasibility items as ≥4 AND Focus groups revealed repeated themes of high feasibility
Pathway Tool	<40% of participants rated all key feasibility items as ≥4 AND Focus groups revealed repeated themes of low to moderate feasibility	40–60% of participants rated all key feasibility items as ≥4 AND Focus groups revealed repeated themes of moderate to high feasibility	>60% of participants rated all key feasibility items as ≥4 AND Focus groups revealed repeated themes of high feasibility

Note: For each feasibility and acceptability outcome, analyses will be stratified by age group (0–2 years and 3–5 years). See Section S6 of the Supplementary Materials for further details of key acceptability and feasibility items.

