#### 2.2.1. Recruitment

A link to an Expression of Interest (EOI) will be sent to ORIGINS participants and community members by The Flourishing Child research team and partner organisations via email. Digital and printed promotional materials will be circulated through online platforms, social media, advertising, and within the local community. The EOI will direct participants to online study information (e.g., eligibility criteria, time commitment, reimbursement). After reviewing this information, participants who wish to take part will complete a screening form and, if eligible, provide electronic informed consent. We aim to recruit participants primarily within the Joondalup and Wanneroo regions over the three-month recruitment period, but we will also accept participants in the wider Perth metropolitan area.

Participants will access the intervention via personal devices. After eligibility screening, all participants will be randomly assigned to either a waitlist-control or intervention group using REDCap’s randomisation module, ensuring that assignment is concealed from researchers until after enrolment [41,42]. Randomisation will be conducted using a 2:1 allocation ratio (intervention/control), stratified by child age, gender, and locality. Participants will be notified of their group assignment and respective study involvement via email. Blinding cannot be implemented in this study, as participants would be aware of their group allocation due to the nature of the intervention; moreover, blinding is not required in this non-clinical trial context. All participants will complete a questionnaire battery at baseline. The intervention group will gain access to the Pathway Tool after completing the Flourishing Check. On completion of the full intervention (i.e., Flourishing Check and Pathway Tool), we will ask intervention group participants to register their interest in participating in focus groups. The waitlist-control group will continue their usual activities. Once data collection has been completed, they will be given access to the Pathway Tool. For ethical reasons, waitlist control groups are preferred over no-treatment controls [43]. Recent trials testing digital parenting interventions have used waitlist controls [44,45,46]. For these reasons, a waitlist control will be used in this study.

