### 2.6. Data Analysis

#### 2.6.1. Primary Outcomes

Acceptability and Feasibility:

The acceptability and feasibility of the Flourishing Check and Pathway Tool will be assessed using a convergent mixed-methods design [52] involving data from questionnaires and focus groups. Additional themes emerging from focus groups, as well as website engagement metrics, will inform future modifications to these tools. Convergent or concurrent mixed methods (also called “parallel”) projects gather quantitative and qualitative data separately, or parallel to each other, and analyse them together. All quantitative and qualitative data will be triangulated and compared for consistency, validity, and credibility. The results will be synthesised to identify themes and recommendations for improving the intervention. Table 3 provides a summary of the data triangulation process and criteria to meet different levels of feasibility and acceptability. This has been created based on the ADePT framework, where 3 categories (green, amber, or red) are used to assess whether a study should progress from a pilot to an efficacy trial [53].

Questionnaires:

The author-developed questionnaires will assess the ease of use, understanding, visual appeal, acceptability of language, readability, functionality, and ease of navigation of the Flourishing Check and Pathway Tool, with higher scores operationalised as greater acceptance. These data will be analysed using descriptive statistics. Additionally, responses to open-ended questions will be subjected to thematic analysis according to best practice, described below [54].

Focus Groups:

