We will aim to recruit N = 600 participants, with n = 400 randomly assigned to the intervention group and n = 200 to the control group. The primary acceptability endpoint is defined as the proportion of participants who rate all key acceptability items as ≥4. This outcome is therefore treated as a binomial proportion. The sample size was chosen to ensure adequate precision around the estimated proportion. Assuming an expected proportion of 60% (based on the predefined acceptability threshold), a sample size of 369 participants, which we rounded up to 400, yields a two-sided 95% confidence interval with a margin of error of approximately ±5%. Unequal allocation (2:1) was intentionally chosen to maximise the amount of information obtained on feasibility and acceptability outcomes in the intervention group, which is the primary focus of the study. The control group remains sufficiently sized to provide a comparator and to inform the design of a future definitive trial. While comparisons between groups will be conducted, these analyses will be considered exploratory, with emphasis placed on the direction and magnitude of effects rather than formal hypothesis testing. After allowing for a loss to follow up of approximately one third in each group, a total sample size of N = 400 would be available for follow-up analysis (intervention group n = 267 and control n = 133). Exploration of any differences between groups in perceived self-efficacy in recognising and supporting flourishing in early childhood and knowledge of programmes and resources, would allow for a small effect size (*d* = 0.30) to be detected using a Mann–Whitney U test, with a power of 80% and alpha of 0.05.

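### Table 3 can return Green, clearing a full-scale RCT without refinement, whatever happened to recruitment and six-month retention

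*Protocol article*

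**What the plan says.** Section 2.6.1 (Primary Outcomes) presents Table 3 as giving the "criteria to meet different levels of feasibility and acceptability". It adds that the three colour categories "are used to assess whether a study should progress from a pilot to an efficacy trial".

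The Amber column of Table 3 reads "Consider Proceeding to Full-Scale Trial Only After Intervention and Protocols Have Been Refined", and the Green column is headed "Green (Proceed to Full-Scale RCT Without Refinement". So the table claims to judge the trial's procedures as well as the tools.

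The four rows cover acceptability and feasibility of the Flourishing Check and of the Pathway Tool. Each cell has two limbs joined by AND. For feasibility, Green is ">60% of participants rated all key feasibility items as ≥4 AND Focus groups revealed repeated themes of high feasibility".

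The plan's figures for trial conduct stand elsewhere:
- Section 2.6.2, Sample Size: "We will aim to recruit N = 600 participants", with an allowance of about one third lost in each group, leaving 267 and 133.
- Section 2.2.1: recruitment is to take place "over the three-month recruitment period".
- Section 2.5: the team monitors whether recruitment targets are met, with no stated consequence for progression.
- Section 4.2: "Insights gained through the feasibility trial will inform amendments to recruitment strategies, methods for maximising adherence and completion rates". No threshold is given, and no link to the colours.

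**The concern.** A randomised pilot is well placed to show whether parents can be enrolled at the needed rate and whether both arms stay to the final assessment. Those two facts largely determine whether a larger RCT of the same design can be run. Here they are planned for and recorded, but the rule that sends the project forward does not use them.

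At stake is a commitment to a full-scale RCT with an unchanged protocol after evidence that the protocol did not recruit or retain. The waitlist arm is the most exposed. After T1 it contributes nothing to Table 3, so heavy loss of controls would leave no trace in the decision.

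**Working it through.** **1. Does any Table 3 input measure trial conduct?** Set each input beside its time of collection (Section 2.1 and Table 1):

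| Input | Collected | Arms |
|---|---|---|
| Flourishing Check ratings | T1, baseline | both |
| Pathway Tool ratings | T2, 1 week | intervention only |
| Focus-group themes | T4, 3 months | intervention only, about 30 parents |
| T5 completion | T5, 6 months | both, **in no row** |
| Number randomised in the window | end of recruitment | both, **in no row** |

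The last input to Table 3 is complete three months before T5 is due, so retention cannot act on a colour. The key items are listed in Supplementary Section S6, which is not shown. Table 3 describes them as items that participants rate, so they cannot stand for a trial-level recruitment or retention count.

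**2. The plan's own figures reproduce.**
- Precision: n = 1.96² × 0.60 × 0.40 / 0.05² = 368.8, so 369, as stated.
- Retention: 400 × 2/3 = 267 and 200 × 2/3 = 133, as stated.
- Power for the Mann–Whitney comparison, normal approximation with efficiency 3/π: Φ(d / √[(1/n₁ + 1/n₂)/(3/π)] − 1.96). With d = 0.30, n₁ = 267 and n₂ = 133, this is Φ(0.30/0.1086 − 1.96) = Φ(0.80) = 78.9%, close to the stated 80%.

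The sample-size arithmetic is not at fault.

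**3. What a shortfall would do, and what Table 3 would show.** The shortfalls are assumptions for illustration.

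| Recruited | Share completing T5 | Left at T5 | Power at d = 0.30 | Effect on Table 3 |
|---|---|---|---|---|
| 600 | 2/3 (as planned) | 267 + 133 | 78.9% | none |
| 600 | 1/2 | 200 + 100 | 66.8% | none |
| 300 | 2/3 | 133 + 67 | 49.8% | none |
| 300 | 1/2 | 100 + 50 | 39.5% | none |

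**4. Does a smaller trial at least make Green harder through the ratings?** Table 3 states no minimum number of raters: 31 of 50 (62%) passes the percentage limb just as 241 of 400 (60.25%) does. The exact binomial probability of exceeding 60%, for a single proportion and ignoring the focus-group limb, is:

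| True share rating all items ≥4 | 400 raters | 200 raters | 100 raters |
|---|---|---|---|
| 70% | 1.000 | 0.998 | 0.979 |
| 65% | 0.979 | 0.920 | 0.828 |
| 55% | 0.019 | 0.067 | 0.134 |

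Halving the intervention group to 200 barely lowers the chance of Green when the tool is well liked. It raises the chance when the true share lies in the Amber range. The percentage limb is no safeguard against under-recruitment.

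**The case against.** The strongest reply is that the primary aim in Section 1.8 is acceptability and feasibility of the Flourishing Intervention, and the rows are its two components. Trial conduct is then handled separately, by monitoring (Section 2.5) and by later amendments (Section 4.2). Improving recruitment methods before a larger trial is compatible with a good rating of the tools. Part of this stands: Section 4.2 is a general forward-looking statement, so the conflict with Green is a tension and not a flat contradiction. But the table's own column headings extend to the protocols and to running the RCT without refinement, and nothing in the article limits Green to the tools.

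Several stronger readings are tempting, and the documents do not support them:
- *Feasibility rests on self-rated items alone.* Every cell also requires focus-group themes. These too are parent reports, so the gap remains.
- *Favourable T2 responders would turn every row Green.* The Flourishing Check questionnaire is completed at T1, so T2 return bears on the percentage limb of the Pathway Tool rows only.
- *The plan sets 369 of 400 as a T2 return target.* The 369 is the sample size for about ±5% precision. No return rate is stated.
- *The plan requires 267 + 133 at T5.* The one-third loss is a planning allowance, and the T5 comparisons are declared exploratory. Only 600 in three months is an aim.
- *A failed pilot passes.* The plan does not define under-recruitment or attrition as failure.

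**Conclusion.** The point holds in this form: the stated progression rule contains no trial-conduct criterion, although it purports to say whether the protocol needs refining. Missing the recruitment aim, or losing far more than one third of either arm, leaves all four rows as they were. In the assumed case of 300 recruited and half lost, 150 of the planned 400 would remain at T5, with about 39% power at d = 0.30, and Green would still be available.

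This follows from the text of Table 3 and the assessment schedule, and does not depend on the illustrative figures. It assumes that Section S6 contains what Table 3 says it contains, namely items that parents rate. It is a weakness in a fully stated rule that is cheap to repair. It is not an error in the sample size, and it does not show that the trial will recruit or retain badly.

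**What to change.** Add two trial-conduct rows to Table 3:
- **Recruitment:** number randomised within the three-month window. Green is anchored to 600, and Amber is a shortfall.
- **T5 completion, each arm separately:** Green is anchored to about two thirds, and Amber is a shortfall in either arm.

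The sponsor should set a Red level for both rows, and any tolerance around the Green figures, before results are seen. The article does not say how rows combine, so add a sentence stating that proceeding without refinement requires these two rows to be Green as well.

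If the rows are not added, the minimum is to relabel Green as covering the intervention tools only, so that it no longer clears the trial protocol.

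The cost is two table rows and a sentence, from data the trial already records. The downsides are that Green becomes harder to reach and that the final colour must wait for T5.

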Focus groups will be used to assess the feasibility and acceptability of the Pathway Tool. Using the approach of Braun and Clarke [54] for thematic analysis, transcripts will be iteratively coded, and codes will be collated into higher-level themes. Transcripts will be reviewed to identify all instances of thematic codes, with codes expanded or collapsed as required. Qualitative data will be analysed using qualitative content analysis [55], assigning a code to each concept using NVivo 14. Similar concepts will be identified and categorised into categories. Data will be analysed using a phenomenological approach (i.e., as a description of experiences as consciously experienced by participants), and narrative themes will be deducted until saturation. The coding process will be guided by the following deductive constructs: intervention acceptability, engagement, and application; mental health and wellbeing experiences; and suggestions for programme revisions.

Engagement metrics:

This data will be used for exploratory purposes to understand how users interact with suggested resources. Exploratory engagement (e.g., clicking resources within the tool or following external links) will indicate whether recommendations are perceived as relevant and worth investigating, supporting acceptability. Recurring engagement, such as saving resources, will indicate sustained interest and practical feasibility of repeated use over time. Collaborative engagement (i.e., copying links to share with others) will further signal acceptability by indicating that users value the content enough to recommend it within their community. These metrics will inform future modifications to the Pathway Tool if the feasibility or acceptability receives an ‘amber’ outcome (see Table 3).

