#### 2.6.3. Triangulation of Data

The totality of the quantitative and qualitative data will be triangulated and interpreted together. We anticipate that the quantitative data will mainly provide insights into how people engaged with the intervention, whereas the qualitative data will provide insights into why they felt/acted this way. We will systematically compare and integrate the findings to assess where they converge or diverge. This will enable a more robust and holistic understanding of the Flourishing Intervention tools and inform further refinements to proceed to the next phase of an effectiveness trial. If the data sets are divergent, and depending on the extent of the divergence, the research team will undertake several strategies to address the divergence, including (a) reconciliation—a re-review of the raw data; (b) bracketing—acknowledging the conflict and/or separating the analyses and contextualising; and (c) complementary explanation—using the divergence to explain the complexity of a phenomenon. Furthermore, engagement metrics will also provide a more objective snapshot of Pathway Tool use if divergent findings are reported between the qualitative and quantitative datasets. For a visual summary of data triangulation, see Figure 3.

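### Table 3's progression rule leaves some combinations of questionnaire result and focus-group themes without a colour, and the article does not say how its four rows combine into one decision

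*Protocol article*

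**What the plan says.** Section 2.6.1 presents Table 3 as the criteria for feasibility and acceptability and says that "3 categories (green, amber, or red) are used to assess whether a study should progress from a pilot to an efficacy trial". The table has four rows: acceptability and feasibility, each for the Flourishing Check and the Pathway Tool. The wording is parallel across rows. For acceptability:

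- Red: "<40% of participants rated all key acceptability items as ≥4 AND Focus groups revealed repeated themes of low to moderate acceptability"
- Amber: "40–60% of participants rated all key acceptability items as ≥4 AND Focus groups revealed repeated themes of moderate to high acceptability"
- Green: ">60% of participants rated all key acceptability items as ≥4 AND Focus groups revealed repeated themes of high acceptability"

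The note to the table adds: "For each feasibility and acceptability outcome, analyses will be stratified by age group (0–2 years and 3–5 years".

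For disagreement between the data sources, Section 2.6.3 says that "depending on the extent of the divergence, the research team will undertake several strategies to address the divergence". It names re-review of the raw data, bracketing and complementary explanation, and adds engagement metrics as a more objective view of Pathway Tool use.

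On the evidence for the Flourishing Check rows, Sections 2.1 and 2.6.1 (opening paragraph) have questionnaires and focus groups covering both tools. The focus-group part of Section 2.6.1 says "Focus groups will be used to assess the feasibility and acceptability of the Pathway Tool", and Section 2.3.4 likewise describes the groups in terms of the Pathway Tool. The Table 1 footnote says that the analysis plan and results of the Flourishing Check questionnaire "will be detailed in a separate paper explaining the development of the Flourishing Check".

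**The concern.** A traffic-light rule is useful if it returns an answer for whatever the data show. Because every Table 3 entry joins two conditions with AND, a row gets a colour only when the two sources agree in one of the listed ways. When they do not, the printed rule returns nothing.

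Progression is this trial's primary conclusion. A row without a colour would have to be graded after the results are known. Those doing so would be the team that hypothesised progression (Section 1.8), and Section 1.7 says that there is no separate endpoint adjudication committee. The same applies when the rows disagree, for instance a Green Flourishing Check with an Amber Pathway Tool.

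**Working it through.** **1. The plan's own figure.** Section 2.6.2 gives 369, rounded up to 400, for a two-sided 95% interval of about ±5% around 60%.

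n = 1.96² × 0.60 × 0.40 / 0.05² = 368.8, rounded up to 369.

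This reproduces. With n = 400 the half-width is 1.96 × √(0.60 × 0.40 / 400) = 4.8 percentage points. The sample size is not in dispute. It matters here because the planning value of 60% is exactly the Amber/Green boundary.

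**2. Coverage of the rule.** The percentage bands alone are exhaustive, since 40% and 60% both fall in Amber. Crossing them with three theme levels gives:

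| Questionnaire | Low themes | Moderate themes | High themes |
|---|---|---|---|
| <40% | Red | Red | none |
| 40–60% | none | Amber | Amber |
| >60% | none | none | Green |

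Assigned: 2 Red + 2 Amber + 1 Green = 5. Unassigned: 9 − 5 = 4. The wording is parallel, so the same four cells are empty in each of the four rows.

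The article does not define three discrete theme levels. If its phrases are instead treated as three fixed labels (low to moderate, moderate to high, high), each colour covers one cell, so 3 of 9 are covered and 6 are empty. Four is the smaller count.

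**3. How near the gap is to the expected result.** Exceeding 60% of 400 means at least 241 participants. Binomial chances:

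| True proportion | n = 400 | n = 267 (at least 161) |
|---|---|---|
| 55% | 0.02 | 0.05 |
| 60% | 0.48 | 0.49 |
| 65% | 0.98 | 0.95 |

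The n = 267 column borrows the plan's retained intervention-group number from Section 2.6.2, to show that fewer respondents change little. These chances concern the questionnaire condition only. The article gives no expectation for the themes, so the chance of landing in an empty cell cannot be calculated.

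**4. Whether Section 2.6.3 fills the cells.** Its three strategies describe how to examine and report divergence, and none ends in a colour. Engagement metrics carry no threshold. Section 2.6.1 uses them to guide modifications once an Amber result has been reached, so it takes the colour as already known.

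**5. Combining rows.** Four rows with three possible colours give 3⁴ = 81 patterns. Only three are uniform (all Red, all Amber, all Green). The other 78 are mixed, and the shown text states no overall decision for them. This counts patterns; it is not a probability.

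**6. Flourishing Check rows.** Set side by side:

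- Section 2.1 (T4) and the opening of Section 2.6.1: focus groups and questionnaires address both tools.
- Section 2.3.4 and the focus-group part of Section 2.6.1: focus groups are described for the Pathway Tool.
- Table 1: the Flourishing Check questionnaire is collected at T1 in this trial, but its analysis plan and results go to another paper.
- Table 3: two of the four rows are graded on that questionnaire and on focus-group themes.

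These statements do not fit together as printed.

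**The case against.** The best defence is that this is a convergent mixed-methods design, in which judgement is intended. Section 2.6.3 foresees disagreement and names ways to handle it, and at least two of the empty cells (above 60% with low themes, below 40% with high themes) are plain divergence. That is a fair account of how findings will be interpreted. It does not settle the colour, and Table 3 is offered as the criteria for the colour.

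A second defence is that, for above 60% with moderate themes, the neighbouring colours are Amber and Green. Both leave progression open, and Section 1.8 hypothesises progression with or without modification. This stands and limits the stakes for that cell. The choice still decides whether the intervention and protocols are refined first. The 40–60% cell with low themes lies between Amber and Red, where the question is whether to proceed at all.

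A third is that Supplement S6 and the full protocol are not shown and might hold a roll-up. That cannot be excluded. S6 is cited only for details of the key items.

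Three stronger readings are tempting and are not supported:

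- Four of nine cells does not mean a 44% risk of no decision. It counts cells, which need not be equally likely.
- The note to Table 3 says that analyses are stratified by age group. A reader might infer eight colours that all have to be combined, but the note does not say that each stratum is graded or decides progression.
- The Flourishing Check rows do not lack evidence altogether. Their questionnaire is collected at T1, and Sections 2.1 and 2.6.1 include the Check in the qualitative work. The fault is a contradiction to reconcile.

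**Conclusion.** The point holds. As printed, the rule for the primary conclusion is not exhaustive: four of nine combinations have no colour in every row, on the assumption that themes are graded low, moderate or high, and six on the label reading. One of the gaps, above 60% with moderate themes, adjoins the study's own planning value. The shown text also gives no way to combine four row colours into one decision; this part is subject to the unseen supplement and full protocol. The article prints the criteria itself, so the incomplete grid is a fault in what is stated and not detail left to another document. The Flourishing Check inconsistency is a separate and lesser matter of reconciling text.

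**What to change.** Let the percentage set each row's colour and let focus-group themes lower it but never raise it, with these triggers:

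| Questionnaire | Low themes | Moderate themes | High themes |
|---|---|---|---|
| <40% | Red | Red | Red |
| 40–60% | Red | Amber | Amber |
| >60% | Amber | Amber | Green |

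This keeps all five cells that Table 3 already assigns and fills the other four. It requires the team to record one theme level per row.

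State, before any acceptability or feasibility results are seen, how the four whole-sample rows combine. Letting the lowest colour govern is one reasonable choice. Report the age-group results descriptively.

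Separately, bring Sections 2.1, 2.3.4 and 2.6.1 and the Table 1 footnote into agreement, so that the two Flourishing Check rows are graded on questionnaire and focus-group data analysed in this trial.

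The cost is a rewording of Table 3, its note and the affected sentences. No extra data are needed if the focus groups cover both tools, as Section 2.1 already says. The downside is less room to argue for a favourable colour once the results are known.
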